### Analysis of exploratory outcomes

The impact of each patient’s iron regulatory genotype (e.g., HFE and TMPRSS6) on the primary and secondary objectives of this study will be assessed by adding an interaction term between genotype and trial arm. If any evidence of an interaction is found (e.g., p < 0.1) then we will also report the stratified results.

### Comparison with control groups at baseline

We will explore differences at baseline in muscle metabolism (from muscle biopsy data) and MRI outcomes (from MRI spectroscopy) between the six Healthy Volunteers (HV), eight non-iron deficient CKD controls (CKD) and 40 iron deficient CKD randomised patients using one-way ANOVA. If data are highly skewed, transformation will be considered (e.g. log transformation). If differences are found, post-hoc analysis will be used to determine where differences lie between groups.

### Statistical considerations

#### Time points

Data recorded outside of these time windows will be included in the primary ITT analysis. However, a sensitivity analysis excluding these data points will be performed to assess if this makes any considerable difference to the model results.

#### Stratification

As the stratification variable was necessarily dichotomised in the design stage, the ANCOVA will also use the dichotomised form. However, sensitivity analysis using the continuous form of the stratification variable will also be performed to ensure substantive conclusions are not highly dependent on the dichotomisation [32].

#### Clustering

It is unlikely that there will be large variation between centres on the primary outcome. Therefore, as this is a relatively small trial with a low number of centres, and some centres with a small number of patients, it is unlikely that any small variation between centres can be accurately modelled, and so centre will not be included in the analysis as a fixed effect. However, variation in centre can be included as a random intercept as a sensitivity analysis without sacrificing many additional parameters, an approach that often has advantages over fixed effect models [33].

#### Missing items in scales and subscales

Questionnaire-based variables to be analysed are the Chalder Fatigue Questionnaire, KDQOL-36 [16], and the Work and Social Adjustment Scale (WSAS). The number (%) with complete data will be reported. Where questionnaire-specific guidance is available for the treatment of missing items in the construction of scales, this will be used. Where such guidance is not available, the King’s Clinical Trials Unit guideline will be followed, i.e. scales will be pro-rated for an individual if 20% or fewer items are missing. For example, in a scale with 10 items, pro-rating will be applied to individuals with 1 or 2 items missing. The average value for the 8 or 9 complete items will be calculated for that individual and used to replace the missing values.

#### Missing baseline data

We expect baseline 6MWD data to be nearly complete, if not fully complete. It is unlikely that excluding any patients with missing baseline data will bias treatment effect estimates or lead to much loss of precision, if any [34], and so a complete case analysis will be undertaken in such a scenario.

#### Missing outcome data

If there are missing data for the primary outcome of 6MWT at 4 weeks, several strategies will be considered. If missingness is below 5%, and missingness is not thought to be isolated to a particular clinically relevant subgroup, then a complete-case analysis (CCA) will be performed [35]. If there is more than 5% missing data, then alternative approaches will be used.

If participants with missing 4-week 6MWT data have post-randomisation variables predictive of missingness of 4-week 6MWT (e.g., 12-week 6MWT) *and* predictive of the 4-week 6MWT values themselves, then a linear-mixed model (LMM) will be performed. This will assume that the missing data is missing at random (MAR) conditional on these post-randomisation variables. Unlike CCA, a LMM can include potentially informative post-randomisation variables without impacting the treatment effect estimates. LMMs also perform similarly to multiple imputation (MI) in such a multivariate scenario (SAP15), whilst not requiring completeness of the post-randomisation auxiliary variables. Although it is unlikely that most participants with missing 4-week 6MWT will have 12-week 6MWT data, there may be other post-randomisation variables associated with 4-week 6MWT and its missingness.

If such post-randomisation variables are not present, patterns of missingness in *baseline* variables will be assessed. If the data is thought to be MAR conditional on observed baseline variables, then a complete-case analysis (CCA) adjusted for variables predictive of missingness will be performed. Under the MAR assumption, this gives unbiased and efficient treatment effect estimates, and generally performs better than alternative methods like MI [34].

If there is evidence of an interaction being predictive of both the outcome and missingness of the outcome (e.g., see “Method for handling the impact of COVID-19” section below), then MI will be used instead of the LMM and adjusted-CCA approaches outlined above. MI has the flexibility to handle both the interaction term and the other variables predictive of missingness and gives an unbiased estimate of the average treatment effect (ATE) in the analysis model [34].

The impact of the MAR assumption in all the above approaches will be assessed via a sensitivity analysis, in which a range of plausible values for the missing outcome data will be assumed, and corresponding treatment effect ranges reported.

For the primary outcome variable (6MWT), there may be cases where the participant has recorded a value for the first test but does not have a value for the second test (which is what will be used in the analyses). As it is likely such values will be generated under a missing-not-at-random mechanism, these values will not be included in the primary analysis.

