**Methods:**

This is a prospective, double-blind multicentre randomised controlled trial (RCT) including 75 non-dialysis stage 3–4 CKD patients with iron deficiency but without anaemia. Patients were randomly (1:1) assigned to either: i) intravenous iron therapy, or ii) placebo, with concurrent recruitment of eight CKD non-iron deficient participants and six healthy volunteers. The primary outcome of the study is the six-minute walk test (6MWT) distance between baseline and four-weeks. An additional exercise training programme for patients in both groups was initiated and completed between 4 and 12 weeks, to determine the effect of iron repletion compared to placebo treatment in the context of patients undertaking an exercise programme. Additional secondary outcomes include fatigue, physical function, muscle strength, muscle metabolism, quality of life, resting blood pressure, clinical chemistry, safety and harms associated with the iron therapy intervention and the exercise training intervention, and hospitalisations. All outcomes were conducted at baseline, 4, and 12 weeks, with a nested qualitative study, to investigate the experience of living with iron deficiency and intervention acceptability. The cohort have been recruited and baseline assessments undertaken.

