### Six minute walk test

The primary endpoint for this study was the change in 6MWT distance between baseline and 4 weeks. The outcome was also performed at 12 weeks following the 8-week exercise training programme. Distance (in metres) was measured during a self-paced, standardised 6MWT conducted around a level, 30.5 m circuit [22]. The walk test was completed twice following sufficient rest (20 min) to allow heart rate to return to resting. The results from the second test were used for analysis.

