### Sample size

#### Primary outcome: 6MWT distance

The choice of endpoint measures to be studied were chosen to provide clinical relevance. Studies that have evaluated the clinically meaningful change in the distance walked on the 6MWT in patients with heart failure [25, 26] indicate that a clinically meaningful improvement in 6MWT distance is between 32 and 45 m. Calculations from the FAIR-HF study [27] and a study in patients with CKD [28] suggested a clinically meaningful improvement in 6MWD of up to 40 m. We have therefore taken this to be the mean clinically important difference (MCID) at the 4-week primary outcome endpoint. An estimated sample size to detect a clinically meaningful difference of 40 m with a SD of 56 m (derived from the higher SD reported by Tang et al. [28]) at 80% power and 5% alpha revealed a requirement of 62 participants. We aimed to recruit at least 70 patients to enable dropouts and ensure that 4-week primary outcome data were collected for at least 62 patients.

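### The reason given for setting aside the first walk in patients without a second walk does not support the rule, and it leaves correctable bias in the primary estimate

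*Protocol article*

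**What the plan says.** The Protocol article, under Six minute walk test, describes the measurement: "The walk test was completed twice following sufficient rest (20 min) to allow heart rate to return to resting". It then fixes the endpoint: "The results from the second test were used for analysis".

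The section Missing outcome data sets out the primary approaches:
- complete-case analysis when less than 5% is missing and the gaps are not confined to a relevant subgroup;
- a linear mixed model (LMM) under MAR, when there are post-randomisation variables that predict both missingness and the week-4 distance;
- otherwise, complete-case analysis adjusted for baseline predictors of missingness;
- multiple imputation (MI) when an interaction is involved.

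It favours the LMM for informative later data: "Unlike CCA, a LMM can include potentially informative post-randomisation variables without impacting the treatment effect estimates". It also plans a sensitivity analysis over a range of plausible values for the missing outcomes.

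The section ends with patients who have a first walk but no second: "As it is likely such values will be generated under a missing-not-at-random mechanism, these values will not be included in the primary analysis".

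**The concern.** The stated reason points the other way. If the second walk is missing because of how the patient was walking that day, the best protection is to condition on something that measures how the patient was walking that day. The first walk is the same test, at the same visit, shortly before. Conditioning on it makes MAR more plausible. Without it, the plan names a mechanism as not at random and then hands those patients to methods that need MAR or low missingness.

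There is also a tension within the section. It looks for post-randomisation variables tied to both missingness and the week-4 value, and offers the 12-week walk as its example while conceding that most such patients will probably not have one. The week-4 first walk fits the description, and every first-walk-only patient has it by definition.

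At stake is attenuation. Inability to repeat the walk may reflect fatigue or poor walking ability. If iron improves walking, more placebo than iron patients would then skip the second walk. The placebo patients who remain are the better walkers, and the estimated difference shrinks toward zero.

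**Working it through.** **The plan's own figure.** Sample size section: "An estimated sample size to detect a clinically meaningful difference of 40 m with a SD of 56 m", "at 80% power and 5% alpha revealed a requirement of 62 participants". With a two-sided 5% test (sidedness is not stated), n per arm = 2 × (1.960 + 0.842)² × 56² / 40² = 30.8, rounded up to 31, so 62 in total. The figure is reproduced and supplies the effect and SD used below.

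**Is missing walk data realistic?** The article expects baseline walk data to be nearly complete, yet Table 4 has 70 values for 75 randomised: 5/75 = 6.7% missing. It does not say how many of those patients had a first walk only, at baseline or at week 4.

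**Model.** Large-sample simulation with 1:1 allocation:
- Second walk: Y2 = 40 × arm + e2, with SD(e2) = 56 m, taken here as the SD given baseline.
- First walk: Y1 = 40 × arm − 15 + e1, with SD(e1) = 56 m and corr(e1, e2) = ρ.
- Skipping: logit P(Y2 missing) = a − s × (W − 20)/56. W is the first walk (with the 15 m added back) or the unseen second walk, and a is set so that 10% are missing overall.

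The 40 m and 56 m come from the article. It gives no value for the rest, so these are assumptions: ρ = 0.7 or 0.9, a 15 m learning effect, s = 1 or 2, and the 10% rate.

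**Analyses.** Without the first walk: difference in mean Y2 among those observed. With it: regress Y2 on arm and Y1 in patients with both, predict the missing Y2, and take the difference in means.

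| Skipping driven by | s | ρ | Missing, placebo / iron | Without first walk (m) | With first walk as auxiliary (m) |
|---|---|---|---|---|---|
| First walk | 1 | 0.7 | 12.9% / 7.2% | 38.1 | 40.0 |
| First walk | 1 | 0.9 | 12.8% / 7.1% | 37.6 | 40.1 |
| First walk | 2 | 0.7 | 14.3% / 5.6% | 35.7 | 40.1 |
| First walk | 2 | 0.9 | 14.3% / 5.6% | 34.6 | 40.1 |
| Second walk | 1 | 0.7 | 12.8% / 7.1% | 37.3 | 38.6 |
| Second walk | 1 | 0.9 | 12.8% / 7.1% | 37.4 | 39.5 |
| Second walk | 2 | 0.7 | 14.4% / 5.6% | 33.9 | 36.7 |
| Second walk | 2 | 0.9 | 14.3% / 5.6% | 33.9 | 38.7 |

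**Attenuation at 10%.** From 40 − 38.1 = 1.9 m to 40 − 33.9 = 6.1 m.

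**Share of bias removed.** If the first walk drives skipping, the auxiliary removes essentially all of it. If the unseen second walk drives it, the share lies between (36.7 − 33.9)/(40 − 33.9) = 46% and (39.5 − 37.4)/(40 − 37.4) = 81%. This is close to ρ² (0.49 and 0.81), so a weaker correlation would remove less.

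**Other rates.** Over 5% to 20% first-walk-only, the estimate is 30.7 to 39.0 m without the first walk and 34.7 to 40.1 m with it.

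**Cases without bias.** With a true effect of zero, with skipping at random, or with skipping that depends on the patient's deviation from the arm mean and so acts alike in both arms, each analysis is right to within 0.1 m.

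**Direct substitution.** Using the first walk in place of the missing second gives 41.2 to 42.8 m at 10% when the first walk drives skipping. It overshoots partly because the 15 m shortfall is charged more often to placebo: for example 15 × (0.143 − 0.056) = 1.3 m.

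**The case against.** **The comparison is with complete-case analysis.** The plan keeps unadjusted complete-case analysis for missingness below 5%. Above that, an LMM may draw on other week-4 measures such as sit-to-stand, muscle strength or fatigue score. This stands, and it reduces the size. In a related simulation (residual SD 76 m, walk-to-walk noise 25 m, 11% and 6% skipping), complete case gave 35.5 m, another auxiliary with an assumed correlation of 0.7 gave 37.6 m, and the first walk gave 39.5 m. The other auxiliary alone thus removed (37.6 − 35.5)/(40 − 35.5) = 47% of the bias. Where complete case does apply, 4% missing in placebo gave 37.9 to 39.8 m, a loss of 0.2 to 2.1 m.

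**A sensitivity analysis is planned.** This stands in part. It addresses departures from MAR, but it leaves the primary estimate as it is, and nothing ties its range to the observed first walk.

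**The sentence may bar only substitution.** On that reading it is sound, since a learning effect makes the first walk a poor stand-in. The wording does not expressly forbid use as an auxiliary. But it keeps the values out of the primary analysis without qualification, so an analyst would probably exclude them altogether. The text needs clarifying on either reading.

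**A stronger reading is tempting:** that the rule itself creates bias, or produces the bias it was meant to prevent. The documents do not support this. Any bias comes from the missing second walk, and the article never says that the exclusion is meant to avoid bias. Nor is there a false-positive risk under the mechanisms examined, because the difference is unbiased when iron has no effect.

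**Conclusion.** The point holds in limited form. A suspected missing-not-at-random mechanism does not justify setting aside the same-visit first walk, and doing so sits badly with the section's own preference for informative post-randomisation variables. The consequence is bias left uncorrected.

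Against complete-case analysis, a true 40 m effect loses roughly 2 to 6 m at 10% first-walk-only. This assumes that poorer walkers skip, that iron works so skipping differs by arm, and that the two walks correlate at 0.7 to 0.9 given baseline. The loss is smaller with other auxiliaries or fewer such patients, and nil under a null effect or when skipping does not act differently by arm. The article gives neither the number of first-walk-only patients nor the correlation, so the practical effect may be small. In every scenario run, the auxiliary was no worse on bias than leaving the first walk out.

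**What to change.** - Keep the second walk as the endpoint, and state that the first walk is not substituted for it.
- State that the week-4 first-walk distance enters the LMM or MI as an auxiliary variable whenever a patient lacks the second walk, including when overall missingness is below 5%. In the LMM it should be an additional response with its own mean in each arm; in MI it belongs in the imputation model only. It should not be a covariate in the ANCOVA, because treatment may affect it.
- Anchor the planned range of plausible values on the first walk, for example as shifts from the value it predicts.
- Report the analysis without the first walk as a sensitivity analysis, and report by arm how many patients had a first walk only.

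The cost is a few sentences and minor programming, using a walk the protocol already requires. The downside is one modelled relation between first and second walks, which can be estimated from patients who did both. The correction is only partial (about 45% to 80% in these runs) if skipping depends on the unseen second walk, which is why the sensitivity range should stay.

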#### Method for handling non-compliance (per protocol/CACE analyses)

The IV iron or placebo administration comprises a single intravenous bolus, given by the unblinded research nurse at the baseline visit (or shortly after) as per the prescription. Non-adherence with treatment is therefore likely to be low, and so no per protocol/CACE analyses will be undertaken.

#### Model assumption checks

Residual plots in all ANCOVA models described above will be checked for normality and homoscedasticity and inspected for outliers and influential points. If any outcome measures have a highly skewed distribution, a transformation of the outcome (e.g., logarithm) may also be considered. The primary outcome (6MWT) is considered likely to be normally distributed.

If there are high degrees of heteroscedasticity then robust standard errors will be considered. If there are any strong outliers then nonparametric (e.g. re-sampling) methods will be considered as an alternative.

#### Method for handling the impact of COVID-19

The characteristics of patients recruited before and after the COVID-19-related study pause will be compared, as suggested by Meyer et al., 2020 [36].

We will first investigate whether the binary variable of being recruited before or after the study break is associated with the primary outcome of 6MWT at 4-weeks. If so, we will see whether this change is additive (e.g., patients post-break walk on average 50 m less than patients pre-break) or multiplicative (e.g. patients post-break walk on average 10% less than patients pre-break). If additive, then it is likely there is no interaction, and so a binary variable indicating their before/after break status will be included as a covariate in the outcome model as a sensitivity analysis. If multiplicative, then this would suggest there may be an interaction. In this case we will perform a sensitivity analysis by adding an interaction term between treatment arm and before/after break status. If there is some evidence of an interaction (e.g., *p* < 0.1) then we will also present the results stratified by before/after break status as a further sensitivity analysis.

The same procedure above will also be performed for the 12-week 6MWT and other outcome variables too. The 12-week 6MWT outcome may be more likely to have an interaction between treatment arm and before/after break status, due to the change in delivery format of the exercise training taking place between weeks 4 and 12. Some of the questionnaire-based outcomes may also be associated with before/after break status.

With regards to missing data, any patients with missing outcome data due to a COVID-19-related site closure will be treated as missing completely at random (MCAR) and excluded from the final primary analysis.

We anticipate that the number of patients becoming infected with COVID-19 during the 4-week window between baseline and the primary outcome timepoint will likely be very low, and so any patients with a missing primary outcome due to COVID-19 infection will be excluded [35]. A similar rationale will also be assumed for all other outcome variables in this case.

If before/after break status is associated with missingness of an outcome and associated with the outcome value itself (but no interaction), then before/after break status will be treated as a baseline variable predictive of missingness as described in the “*Missing outcome data*” section above and included as a covariate in a CCA.

If before/after break status is associated with missingness of an outcome, *and* there exists an interaction between this status and the treatment arm, then MI will be used to handle missing data in the primary analysis, as described in the “Missing outcome data” section above. The imputation model will include this interaction as a covariate, together with other variables predictive of missingness and of the outcome.

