### Follow-up visits

Patients completed follow-up measures at 4 weeks (± 4 days) and 12 weeks (± 14 days) after treatment.

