### Safety and monitoring of the intervention

Serious adverse events were identified and documented on the eCRF at routine visits, based on participant reports and primary or secondary care reports. In addition, episodes of infection requiring hospitalisation and other infection episodes and cases of vascular access thrombosis were documented. In addition, haemoglobin, ferritin, platelet levels, and other laboratory measurements detailed above were monitored.

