### Analysis of secondary outcomes

The ANCOVA described above for the primary outcome will also be performed for the 6MWT distance (metres) at 12 weeks, and for the other secondary endpoints described earlier. In each case, the baseline value of the variables and the binary stratification factor will be used as covariates.

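### The 4-week argument for excluding outcomes lost to COVID-19 infection is extended without further reason to the 12-week secondary outcomes

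*Protocol article*

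**What the plan says.** All references are to the protocol article.

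- **Reason for the rule** (Method for handling the impact of COVID-19): the number of patients infected "during the 4-week window between baseline and the primary outcome timepoint will likely be very low".
- **The rule** (same section): "any patients with a missing primary outcome due to COVID-19 infection will be excluded".
- **Its extension** (same section): "A similar rationale will also be assumed for all other outcome variables in this case". No time point is attached to this sentence.
- **Follow-up times** (Follow-up visits): "Patients completed follow-up measures at 4 weeks (± 4 days) and 12 weeks (± 14 days) after treatment".
- **12-week analysis** (Analysis of secondary outcomes): the primary ANCOVA "will also be performed for the 6MWT distance (metres) at 12 weeks, and for the other secondary endpoints described earlier". Its covariates are the baseline value and the ferritin stratum, with no week-4 term.
- **General missing-data rule** (Missing outcome data), written for the 4-week 6MWT: complete-case analysis is reserved for missingness under 5% that is not confined to a relevant subgroup. Beyond that, "If there is more than 5% missing data, then alternative approaches will be used". The first alternative is a linear mixed model, chosen because "Unlike CCA, a LMM can include potentially informative post-randomisation variables without impacting the treatment effect estimates". A sensitivity analysis over plausible missing values is attached to the approaches listed in that section.

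**The concern.** The only support for the exclusion is that few infections will fall in a short window. At 12 weeks the window is longer, so the support weakens exactly where the rule is extended. The rule has no upper limit: patients with an infection-related missing value leave the 12-week comparison whatever their number.

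Patients infected after week 4 will usually have week-4 values, and these carry information about the missing week-12 value. The exclusion leaves it unused. The sensitivity analysis over plausible missing values is tied to the methods in Missing outcome data and is not stated to reach exclusions made under the COVID-19 section.

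At stake are the 12-week secondary comparisons: 6MWT, muscle strength, STS60, fatigue, WSAS and quality of life. The 4-week primary analysis is not affected.

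**Working it through.** **1. The plan's own figure.** No infection rate or expected number of exclusions is given, so none can be reproduced. The sample size, whose inputs are used in step 4, does reproduce: 2 × (1.960 + 0.842)² × 56² / 40² = 30.8, hence 31 per arm and 62 in total, as stated (two-sided 5% assumed).

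**2. Which outcomes the reason fits.** The overview of the trial schedule (Table 2) places MRI spectroscopy and muscle biopsy at baseline and week 4 only, so the 4-week reason fits them. The 6MWT, strength, STS60 and the three questionnaires are repeated at week 12. For these the window is 12 / 4 = 3 times as long, or up to 14 weeks with the visit allowance.

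**3. Expected exclusions.** Let p be the assumed proportion losing an outcome to infection per 4 weeks, constant over time, with N = 75 randomised. Week 4: 75p. Week 12: 75 × [1 − (1 − p)³].

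| Assumed p | Week 4 | Week 12 | Week 12, % of 75 |
|---|---|---|---|
| 1% | 0.75 (0.8) | 75 × 0.0297 = 2.2 | 3.0% |
| 2% | 1.5 | 75 × 0.0588 = 4.4 | 5.9% |
| 4% | 3.0 | 75 × 0.1153 = 8.6 | 11.5% |

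As a yardstick, 5% of 75 is 3.75, so four or more missing exceeds the threshold that the plan sets for the 4-week 6MWT. The binomial probability of four or more is 0.7% at week 4 and 18% at week 12 for p = 1%, and 6% and 65% for p = 2%.

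These are upper-end figures. One rate is applied to all 75, although some were recruited before the pause. The formula also counts every event in the 12 weeks as a lost week-12 value, although a patient infected early may still attend at week 12. Visits delayed beyond the window stay in the primary intention-to-treat analysis (Time points).

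**4. Effect on the estimate.** A simulation used 37 patients per arm, a true difference of 40 m at both times, SD 56 m, an assumed week-4/week-12 residual correlation of 0.7 and 4,000 replicates. The log-odds of a missing week-12 value were logit(base rate) − d × (week-4 residual / 56). With d = 0 missingness is unrelated to week 4; with d = 1 poorer walkers are more often missing. Exclusion compares the observed week-12 means. The week-4-informed estimate fits week 12 on arm and week 4 among those observed, then takes b(arm) + b(week 4) × the difference between arms in mean week-4 value over all patients.

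| Base rate, iron / placebo | d | Full data | Exclusion (SE) | Using week 4 (SE) |
|---|---|---|---|---|
| 10% / 10% | 0 | 39.6 | 39.6 (13.7) | 39.6 (13.3) |
| 10% / 10% | 1 | 40.3 | 40.3 (13.9) | 40.4 (13.7) |
| 15% / 5% | 0 | 40.2 | 40.1 (13.9) | 40.2 (13.6) |
| 15% / 5% | 1 | 40.5 | 44.2 (14.0) | 40.5 (13.8) |

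Only the last row shows bias: 44.2 − 40.5 = 3.7 m on a 40 m effect. It needs both an imbalance between arms and dependence on week-4 performance.

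**The case against.** The best defence is that the consequences are minor. The rule removes only those whose outcome is missing, and only from the analysis of that outcome. Delayed visits are kept, part of the cohort was recruited before the pause, and the bias in step 4 needs conditions that the documents do not establish. All of this stands and limits the size of the point. The full analysis plan is not shown and may treat the 12-week outcomes more fully, but the article does state the extension, and its reason does not fit.

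Some stronger readings are tempting and are not supported:

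- *The 12-week comparison is restricted to patients who stayed well.* An infected patient who is assessed, even late, remains in.
- *The plan calls infection-related missingness completely at random.* It uses that label for site closures; the infection rule rests on small numbers.
- *The plan breaks its own commitment to a mixed model.* The 5% threshold and the mixed model are written for the 4-week 6MWT. The passage following the COVID-19 rules carries missing-data methods to other outcomes only through before/after-break status. Using week-4 data at week 12 extends the plan's logic and was not promised.
- *Gym attendance between weeks 4 and 12 raises exposure.* Home training online was offered because of COVID-19, and how many patients chose it is not stated.
- *Infection is likely to differ by arm.* Safety monitoring does record "episodes of infection requiring hospitalisation and other infection episodes", but nothing in the documents suggests that COVID-19 infection would be unequal in a blinded comparison.
- *The 4-week primary rule must change too.* The argument turns on 4 weeks against 12, so it does not reach the primary.

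**Conclusion.** The point holds for the 12-week secondary outcomes and no further. The exclusion is justified by a 4-week window and applied to a window three times as long without a reason of its own. Under a constant assumed risk of 1% to 4% per 4 weeks, expected exclusions rise from 0.8–3.0 to 2.2–8.6 of 75, and the true numbers are probably lower. Bias is likely to be small: none appeared in the simulation when missingness was balanced across arms or unrelated to week-4 values, and it was about 4 m on 40 m when both conditions failed. Otherwise the loss is a little precision (SE 13.7 against 13.3 m at 10% missing per arm). These sizes rest on assumed rates, an assumed correlation of 0.7 and the 56 m SD from the sample-size section. The change is worth making because the alternative was at least as precise in every scenario and rests on a weaker missing-data assumption.

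**What to change.** 1. Limit the exclusion for COVID-19 infection, and its rationale, to outcomes measured at 4 weeks.
2. For 12-week outcomes, treat infection-related missing values as missing at random in a linear mixed model with baseline, stratum and week-4 values. The week-4 value should enter as a repeated outcome; as a covariate it would adjust away part of the treatment effect.
3. State that the sensitivity analysis in Missing outcome data, over plausible missing values, includes these patients.
4. Report by arm how many patients lack each 12-week outcome because of infection.
5. Leave the rule for the 4-week primary outcome unchanged.

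The cost is a short extra model specification, because Analysis of secondary outcomes now gives ANCOVA on baseline and stratum only. No new data are needed, since the week-4 measurements are already in the schedule.
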